### Duration of the Study

The three intervention sessions will take place weekly so the duration of the study therapy sessions will extend over four weeks (see Figure 1). Eight weeks after the last study therapy session, the last follow-up measurement will take place (online). Longer follow-up intervals (e.g., at three or six months) were not implemented in this trial due to feasibility constraints and methodological considerations. Since participants continue to receive non-standardized CBT throughout and beyond the follow-up period, longer intervals would likely introduce greater variability in treatment exposure, making it more difficult to attribute outcomes specifically to the experimental intervention. Shorter follow-up intervals were therefore chosen to maintain a clearer link between the experimental intervention and outcome assessments. The duration of the sessions in both experimental and control conditions is comparable (60 – 90 minutes) to control for time and therapist contact. The study procedure is also presented in Figure 1. Participants who take part in all sessions of the study will receive €50 as compensation for their time investments.

**Figure 1 f1:**
[figure not shown]
Study Procedure

### Measures

#### Primary Outcome

Changes in Depressive Symptom severity, assessed by the Beck Depression Inventory-II (BDI-II; Beck et al., 1996) will be the primary outcome. The BDI-II is a 21-item self-report instrument assessing depressive symptoms. The items are rated from 0 to 3, with 3 for the most depressed mood. A score 0 – 13 indicates minimal depression, 14 – 19 mild depression, 20 – 28 moderate depression and 29 – 63 severe depression. The BDI-II will be measured before randomization (baseline), one week after the last session (post-intervention) and 4 weeks and 8 weeks after the last session (follow-up). The BDI-II was chosen as the primary outcome due to its strong psychometric properties, sensitivity to change, and feasibility for repeated online assessments, thereby minimizing participant burden and facilitating efficient data collection.

#### Secondary Outcomes

We will use the following measures at every measurement (before randomization (baseline), just prior to every session, one week after the last session (post-intervention) and four weeks and eight weeks after the last session (Follow-up 1 and 2)): Depressive symptom severity, measured by the depression module of the Patient Health Questionnaire (PHQ-9; Kroenke et al., 2001); Rating (0 – 100) of the belief that the core beliefs captured in the baseline session are true; Rating (0 – 100) of the emotions that are associated with the memories and core beliefs captured in the baseline session; Rating (0 – 100) of the burden of the memories for the patient. The PHQ-9 was included alongside the BDI-II to allow for convergent validation of depressive symptom trajectories. In addition, due to its brevity and ease of administration, the PHQ-9 is used at each study session, making it possible to assess depressive symptoms at more frequent time points than with the BDI-II. This enables a more fine-grained analysis of symptom changes across the intervention period.

The following measures will be administered before randomization (baseline), one week after the last session (post-intervention) and four weeks and eight weeks after the last session (Follow-up 1 and 2): *Repetitive negative thinking*, measured by the Perseverative Thinking Questionnaire (PTQ; Ehring et al., 2011); *Emotional capabilities*, measured by the Self-Assessment of Emotional Capabilities (SEK-27; Berking & Znoj, 2008); *Self-compassion*, measured by the short version of the German Self-Compassion Scale (SVS-SV; Hupfeld & Ruffieux, 2011); *Self-efficacy*, measured by the German global self-efficacy expectancy scale (SWE; Jerusalem & Schwarzer, 1999); *Beliefs about emotions*, measured by the German version of the Emotion Beliefs Questionnaire (EBQ; Grüning et al., 2021); *Self-esteem*, measured by the German version of the Rosenberg Self-Esteem Scale (RSES; von Collani & Herzberg, 2003). At post-intervention, we will measure *satisfaction with treatment*, measured by the German patient satisfaction questionnaire (ZUF-8; Schmidt et al., 1989) adapted for the study as well as the *working alliance* between patient and study therapist, measured by the working alliance inventory (WAI; Wilmers et al., 2008). At the post-intervention assessment, the patients will also be asked in an open-response format, to what extent they think they have benefited from the study.

#### Additional Measures

To evaluate possible confounding variables, the following constructs are measured: *Childhood Trauma*, measured by the Childhood Trauma Questionnaire (CTQ; Bernstein & Fink, 1998), which will be administered during the baseline measurement as ImRs interventions were originally developed for intrusive memories following traumatic events; *Time of intervention*: Time interval (in days) between the participants’ regular CBT session and the study therapy session for each of the three intervention sessions; *Comorbid disorders*, as measured with the SCID-5-CV interview at the outpatient clinic before the start of the study;

*Therapeutic techniques* used in patients’ routine therapy, as well as the *amount of regular therapy sessions* received during the study period, will be recorded via a questionnaire sent to the treating therapists at the outpatient clinic after the patient has completed the final follow-up assessment (FU2). The CBT conducted alongside the study intervention is part of routine clinical care and not part of the study protocol. It follows a naturalistic format without a standardized manual, predefined number of sessions, or fixed structure. Consequently, the dose and content of CBT may vary between participants. To monitor potential overlap with imagery-based methods, the therapist questionnaire includes items assessing whether, and to what extent, imagery techniques or imagery rescripting were used during the course of therapy.

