### Participants

Inclusion criteria are (a) meeting the diagnostic criteria for a current major depressive disorder (MDD), as assessed with a SCID-5-CV interview (patients with comorbid disorders are eligible to participate), (b) age 18 years or older, (c) sufficient proficiency of German language to complete questionnaires. Patients are excluded from participation if they are at high risk of suicidality, defined as the presence of acute suicidal ideation with concrete plans or intent. This is assessed during the standard intake procedure at the outpatient clinic where the study is conducted. Diagnostic information is based on the initial clinical interview (SCID) conducted by the therapist at the outpatient clinic; no additional study-specific diagnostic assessment will be conducted. Participants are informed about the study at the beginning of their treatment but may enrol at any point during their ongoing CBT. The number of standard CBT sessions completed at study entry will be documented and reported. It is important to note that CBT is delivered as part of routine care in the outpatient clinic and is not part of the experimental study protocol. No efforts are made to standardize or influence the content, structure, or dose of the ongoing CBT. However, information on the number of CBT sessions and the use of imagery techniques during therapy will be collected post-hoc via therapist questionnaires.

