### Data Analyses

To address the longitudinal nature of our data and potential missing values, we will employ a multilevel approach. This method allows us to model individual trajectories of change over time while accounting for between-person differences. The multilevel model will include time as a within-subject factor and condition as a between-subject factor. The interaction effect between time and condition is of main interest, as it will indicate whether the rate of change in depressive symptoms differs between the intervention and control group. All primary analyses will be conducted using an intention-to-treat (ITT) approach, including all randomized participants. Missing data will be handled using mixed-effects models, which are robust to missingness under the assumption of missing at random. Analysis will be conducted in R (R Core Team, 2025). In case of substantial differences between conditions in demographic or any of the potentially confounding variables listed previously (e.g., number of CBT sessions before intervention), the variable(s) will be added as covariates to the model. For the analysis of secondary outcomes (e.g., repetitive negative thinking, emotional capabilities, self-compassion, self-esteem), we will employ a similar multilevel modelling approach. Each secondary outcome will be analysed separately, with time and condition as predictors, and the time-by-condition interaction as the primary effect of interest. Given the number of secondary outcomes, we will apply a correction for multiple testing to mitigate the risk of Type I errors across models. Effect sizes will be reported alongside *p*-values to aid interpretation. Results will be treated as exploratory, and full model outputs (including corrected and uncorrected *p*-values) will be provided in the supplementary material to ensure transparency. This will allow us to examine how these outcomes change over the course of the study and whether these changes differ between the ImRs and control conditions.

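### The therapist questionnaire on routine CBT is triggered by the patient completing FU2, so as written co-intervention and contamination are compared only among FU2 completers

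*Protocol article*

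**What the plan says.** The Additional Measures section opens with "To evaluate possible confounding variables, the following constructs are measured". Among these constructs are the techniques used in routine therapy and the amount of regular therapy during the study. Both come from "a questionnaire sent to the treating therapists at the outpatient clinic after the patient has completed the final follow-up assessment (FU2"). The Participants section confirms the source and adds no other trigger: "information on the number of CBT sessions and the use of imagery techniques during therapy will be collected post-hoc via therapist questionnaires".

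The Data Analyses section links these variables to the primary model: "In case of substantial differences between conditions in demographic or any of the potentially confounding variables listed previously", then "the variable(s) will be added as covariates to the model". Its example is the "number of CBT sessions before intervention". The same section states: "All primary analyses will be conducted using an intention-to-treat (ITT) approach, including all randomized participants". Its only method for missing data is the mixed model under missing at random.

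**The concern.** The questionnaire is answered by the treating therapist, so a patient's absence from FU2 does not make the information unobtainable. Tying dispatch to FU2 completion still leaves it uncollected for non-completers if the text is followed.

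Two things are at stake.

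- **Interpretation.** The trial asks what ImRs adds to CBT that is neither manualised nor fixed in dose. The questionnaire is the only source the article describes for in-study CBT dose and for imagery methods used in routine therapy. A comparison of these by arm among FU2 completers is a comparison of groups selected after randomisation.
- **The primary model.** The covariate rule covers any listed confounder, so these variables are eligible. A mixed model under missing at random deals with missing outcomes, not with a missing patient-level covariate. If incomplete rows are deleted, every BDI-II value of that patient goes, including values that were observed.

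**Working it through.** **1. The plan's own power figure.** The Sample Size section gives 85–90% power at about 60–70 patients for β = 0.25, with four time points and a random intercept. It does not give alpha, the SD, the ICC or the scale of β, so the figure cannot be checked strictly. Assume two-sided alpha 0.05, total SD 1 and ICC 0.5, and read β as a slope per measurement step. The SD of a patient's slope is then √((1 − 0.5)/5), and power is 86.5% / 89.5% / 91.1% at N = 60 / 66 / 70, close to the stated range. If β is instead the FU2-minus-baseline contrast, the same assumptions give 17% at N = 66. The steps below use only the plan's lower anchor, 85% at N = 60.

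**2. Patients without questionnaire data.** No dropout rate is stated, so 10/20/30% are assumptions. 66 × 0.10 / 0.20 / 0.30 = 6.6 / 13.2 / 19.8, that is 7 / 13 / 20 patients without data and 59 / 53 / 46 with data.

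**3. What row deletion removes.** Take 13 patients who leave after the post-intervention assessment (two BDI-II values each) and 53 with all four.

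- Without the covariate: 53 × 4 + 13 × 2 = 238 rows, 66 patients.
- With a covariate missing for the 13: 53 × 4 = 212 rows, 53 patients, all FU2 completers.

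Fitting both models to an artificial data set gave these counts.

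**4. Power lost to deletion, separated from dropout itself.** Non-completers have no FU2 value in any analysis, so the fair comparison is deletion against a mixed model that keeps all 66. With power = Φ(ncp − 1.960), the anchor gives ncp = (1.960 + 1.036) × √(N/60), which is 88.2% at N = 66 with no dropout.

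Worked case: 13 non-completers with a baseline value only, ICC ρ = 0.5, FU2-minus-baseline contrast.

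- Variance (up to a constant) with all 66 kept: (1 − ρ²)/53 + (1 − ρ)²/66 = 0.75/53 + 0.25/66 = 0.01794.
- Variance with no dropout: 2(1 − ρ)/66 = 0.01515.
- Effective N = 66 × 0.01515/0.01794 = 55.7; ncp = 2.996 × √(55.7/60) = 2.89; power 82.3%.
- After deletion, N = 53: ncp = 2.996 × √(53/60) = 2.82; power 80.4%.
- Loss due to deletion: 1.9 points.

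Repeating this with ICC 0.5, 0.6 and 0.7, categorical or linear time, exit after baseline, post-intervention or FU1, and equal dropout in both arms gives:

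| Assumed FU2 non-completion | Patients left after deletion | Power after deletion | Power keeping all 66 | Added loss (points) |
|---|---|---|---|---|
| 10% | 59 | 84.4% | 84.9–86.1% | 0.5–1.7 |
| 20% | 53 | 80.4% | 81.5–84.2% | 1.1–3.8 |
| 30% | 46 | 74.7% | 76.4–81.5% | 1.8–6.9 |

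**5. Bias.** Large-sample simulation (ICC 0.5, about 15–18% dropout after post-intervention) compared deletion with the mixed model on all patients, with no true effect. When dropout depended on lack of early change in the ImRs arm only, deletion gave −0.11 SD against 0.00. When the same mechanism acted in both arms, or dropout depended on the post-intervention score level, the bias was at most 0.01 SD.

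**The case against.** The sentence in Additional Measures may only be about timing. Sessions during the study can be counted only once the study period is over, and the text does not say that non-completers are skipped. The full protocol may cover them. This is a fair caution, but the article does fix a trigger, and that trigger is a patient event where a date would serve. Followed literally, it loses data that are easy to obtain.

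A reader might infer that the primary analysis is a completer analysis. The documents do not support that. It would need a substantial arm difference on one of these variables and deletion of incomplete rows, which the Data Analyses section does not state; imputing the covariate would keep every patient. The one covariate named as an example is also unaffected, since "The number of standard CBT sessions completed at study entry will be documented and reported".

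A reader might also set 88% power at N = 66 against 84% / 80% / 75% after deletion and charge the whole drop to the questionnaire. Most of it is due to dropout, which no trigger can repair.

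Nor are these the only data on concurrent care. Sessions at entry and the interval between regular CBT and each study session are recorded too, and neither is said to depend on FU2. Finally, nothing in the article shows that patients who leave the study also change or end their routine therapy.

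**Conclusion.** The point holds in a limited form and is worth correcting. The firm part needs no modelling: as written, in-study CBT dose and imagery use are not collected for patients who never complete FU2, so the arm comparison of both is confined to a post-randomisation subset.

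The consequence for the primary model is conditional on such a covariate entering and on row deletion. Then 59 / 53 / 46 of 66 patients remain at an assumed 10/20/30% non-completion, and the added power loss is roughly 1–2 / 1–4 / 2–7 points. Bias could be anywhere from negligible to about 0.1 SD in the scenarios tried, depending on a dropout mechanism the article cannot foresee.

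A related weakness in the covariate rule does not depend on missing data. CBT dose and imagery use during the study arise after randomisation. If ImRs influences them, adjusting for them can remove or distort part of the treatment effect even when every form is returned. Completing the questionnaires is therefore not a sufficient repair.

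**What to change.** 1. In Additional Measures, replace the trigger: the questionnaire goes to the treating therapist of every randomised patient at the scheduled FU2 date, whether or not sessions or assessments were completed. From the Design section this is 3 + 8 = 11 weeks after the baseline session.
2. Report CBT dose and imagery or ImRs use by arm for all randomised patients, with the number of forms not returned.
3. In Data Analyses, limit covariates in the primary model to baseline variables. Use the questionnaire variables descriptively or in sensitivity analyses, and say there how missing values are handled. The interval between regular CBT and study sessions is also measured after randomisation and falls under the same restriction.

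The cost is a few sentences and some extra forms for therapists at the same clinic (7 / 13 / 20 under the assumed rates). No additional patient contact is needed.

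### Imagery use in routine CBT is recorded only after FU2, over two unreconciled time windows, yet the covariate rule could bring it into the primary model

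*Protocol article*

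**What the plan says.** **Timing and content of the form.** Additional Measures says that techniques used in routine therapy are obtained from the treating therapists by a form "sent to the treating therapists at the outpatient clinic after the patient has completed the final follow-up assessment (FU2"). For imagery, "the therapist questionnaire includes items assessing whether, and to what extent, imagery techniques or imagery rescripting were used during the course of therapy". The stated purpose is to monitor overlap with imagery-based methods. Participants describes the same collection: "information on the number of CBT sessions and the use of imagery techniques during therapy will be collected post-hoc via therapist questionnaires".

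**Time window.** The sentence in Additional Measures that introduces the form names techniques and then the amount of regular therapy "received during the study period, will be recorded via a questionnaire sent to the treating therapists". The imagery items have a different window: whether "imagery techniques or imagery rescripting were used during the course of therapy".

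**Entry into the trial.** Participants says that patients "may enrol at any point during their ongoing CBT". What is recorded about earlier CBT is its quantity: "The number of standard CBT sessions completed at study entry will be documented and reported". Earlier imagery rescripting (ImRs) is not an exclusion criterion, and the trial does not try to influence what happens in routine CBT.

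**Use in the analysis.** Additional Measures presents its list as potential confounders. Data Analyses says that demographic variables and listed potential confounders that differ substantially between conditions become covariates. Its own example is the number of CBT sessions before the intervention.

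**The concern.** Imagery work with the regular therapist before study entry is a baseline characteristic. It can serve as a covariate or define a subgroup without disturbing the randomised comparison. Imagery work after randomisation is contamination. It may depend on the assigned arm, and a model that conditions on it no longer estimates the intention-to-treat effect.

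Dependence on arm is plausible here. Every patient has three distressing memories and the related core beliefs drawn out in the introductory session, but only the ImRs arm goes on to rescript them in the study sessions. Regular therapists may respond differently in the two arms. The document gives no data on whether they do.

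The article describes one late form, does not say clearly which period it covers, and has a rule that can turn its answers into covariates. At stake is what the adjusted primary estimate means, and how clearly contamination can be described when the result is read.

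**Working it through.** The point concerns the timing of a measurement, and the plan gives no figure for it. The first two steps therefore set the passages side by side. The last two are illustrations.

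**1. Two readings of the window.**

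| Reading of the imagery items | Use before entry | Use after randomisation |
|---|---|---|
| Whole course of therapy | included, not separated as described | included, not separated as described |
| Study period only | not recorded | recorded |

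On the first reading the variable is partly post-randomisation; on the second, wholly so. Neither gives a pre-randomisation measure of imagery use. Sessions fall in weeks 1 to 3 after baseline and FU2 comes 8 weeks after the last session (Design). The therapist therefore looks back about 3 + 8 = 11 weeks to the introductory session, and further to the start of CBT.

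**2. When the covariate rule would act.** Let p be the share with ImRs before entry, the same in both arms in expectation. Let a and c be the shares with ImRs in routine CBT after randomisation in the ImRs and control arms. If the two exposures are independent, the expected difference in ever-use is

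[1 − (1−p)(1−a)] − [1 − (1−p)(1−c)] = (1−p)(a − c).

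With p = 20%, a = 0 and c = 20% (all assumed), ever-use is 1 − 0.80 = 20% in the ImRs arm and 1 − 0.80 × 0.80 = 36% in controls. An imbalance beyond chance thus reflects use after randomisation, and that imbalance is what would trigger adjustment.

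**3. What adjustment could do.** Let D be the benefit of the study ImRs sessions and g that of ImRs in routine CBT, both additive. The unadjusted difference is D + g(a − c). Adjusting for post-randomisation use gives about D in the best case, where nothing else drives both that use and the outcome. With g = D and a = 0, the unadjusted difference is D(1 − c):

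| c (assumed) | Unadjusted / D | Adjusted / unadjusted |
|---|---|---|
| 10% | 0.90 | 1/0.90 = 1.11 |
| 20% | 0.80 | 1/0.80 = 1.25 |
| 30% | 0.70 | 1/0.70 = 1.43 |

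If therapists choose imagery according to how the patient is doing, the adjusted figure is not D either, and the direction of its error is unknown.

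**4. Context: contamination and power.** Sample Size states 85–90% power at 60–70 patients for β = 0.25, without alpha, residual SD or random-intercept variance, so the figure cannot be firmly reproduced. Assume two-sided alpha 0.05, total SD 1, intraclass correlation (ICC) 0.5 and β as a slope per step over four equally spaced times. Then SE = √[(1 − ICC)/5 × 2/n], with n per arm. Power is 86.5%, 89.5% and 91.1% at N = 60, 66 and 70. If β is instead a single 0.25 SD contrast at FU2, power at N = 66 is 11–62% for ICC 0–0.9.

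Under the slope reading at N = 66, SE = √(0.1 × 2/33) = 0.0779. Replacing 0.25 by 0.25(1 − c) lowers power from 89.5% to 82.4%, 72.9% or 61.3% for c = 10%, 20% or 30%. That loss comes from the contamination itself; a better form would not change it.

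**The case against.** The form's items are not shown. A form sent once after FU2 can still ask separately about the time before and after study entry, and a journal article often leaves such layout to the full protocol. On the study-period reading, contamination is measured on its own and only a baseline characteristic is missing. The naturalistic setting is deliberate, and the Discussion concedes that parallel CBT may shrink the effect and that additive interpretations are exploratory.

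Most of this stands, and it rules out three stronger conclusions that a reader might draw.

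- **That earlier exposure and contamination can never be told apart.** The text supports only that they are not separated as described.
- **That no sensitivity analysis is possible.** A patient reported as having had no imagery work over the whole course is unexposed in both periods, and the share with any use bounds contamination from above. However, a group selected in this way is partly defined after randomisation, so comparing arms within it is not protected by randomisation.
- **That a null result could not be interpreted.** The intention-to-treat comparison includes all randomised patients and needs nothing from this form. Earlier exposure is balanced in expectation.

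Attenuation factors of the form (1−p)(1−c), such as 0.90 × 0.90 = 0.81 or 0.80 × 0.80 = 0.64, do not measure this defect either. They describe dilution that remains however the form is worded, and p and c are assumed.

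The objection does not answer two things. The paragraph uses two windows without reconciling them, and the covariate rule does not confine itself to variables fixed before randomisation.

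**Conclusion.** The concern holds in limited form. As described, imagery and ImRs use in routine CBT is collected only after FU2, over an unclear window. Use before entry is either mixed with later use or not recorded. The main consequence runs through the covariate rule, which could put a variable that is wholly or partly post-randomisation, and possibly affected by arm, into the primary model. Without that adjustment the primary comparison is unaffected.

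The document gives no rate of imagery use in routine CBT, so the size is unknown. For assumed contamination of 10–30% of controls with equally effective ImRs and none in the other arm, the adjusted estimate could exceed the unadjusted one by a factor of 1.11 to 1.43. This requires the rule to be triggered and the additive model above to hold. If the form already separates the periods, one clarifying sentence settles the measurement part. The covariate rule would still need its restriction.

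**What to change.** 1. The treating therapist answers the imagery and ImRs items once before randomisation, for sessions to date.
2. Limit the FU2 form to the time from randomisation to FU2, and use that one window throughout Participants and Additional Measures.
3. State in Data Analyses that only the pre-randomisation answer may serve as a covariate or define a subgroup or sensitivity analysis. Report use after randomisation by arm, descriptively, as contamination.
4. An analysis leaving out patients with ImRs before entry would keep the randomised comparison, because the group is fixed beforehand. With fewer than 66 patients it would be less precise, and should be labelled supportive.

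The cost is one short form at referral, when the therapist already hands out the study information, plus a reworded time window and one sentence in the analysis section. No extra visit or staff is needed.
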